### Participants recruitment

150 adolescents will be recruited through flyers, advertisements on the lab website, mental health adolescent units, and social media platforms advertising the study in Geneva and Haifa. Study adverts will direct interested participants and their families to a Qualtrics page. There, they can review the study information, may choose to undertake screening and provide consent to be signed by the parent or legal guardian using the provided links. Regarding the recruitment site in Geneva, participants will be provided with contact information for local mental health and crisis support services in the information form to provide adequate information in case participants require care and support. Direct contact between the participant and the study team will not be required during recruitment and study enrolment. After signing the consent form, families will be redirected to online questionnaires to screen participants’ suitability for inclusion. Eligible participants will be redirected to a short contact form to collect their name, phone number and email address to be contacted by the research team and set up an appointment at the University of Geneva (Switzerland) or at the University of Haifa (Israel). Personal information will be stored in our secure system on university servers. Adolescents recruited will be provided with adapted study information and will sign an assent form before starting the baseline assessment. This study has been approved by the Ethics Board of the University of Geneva (CUREG) and by the Institutional Review Board (IRB) of the University of Haifa.

### Sample size

A power analysis indicates 26 participants per group are needed given a repeated measure ANOVA design looking at a 3-within (time of assessment) x 3–between (training conditions) interaction, Hedge’s G of -0.25, alpha level of 0.05 and power of 0.8, and a repeated-measure correlation of 0.70 (test-retest correlation on SCARED from Behrens et al., [73]; and Hedge’s G from the meta-analytic work of Wang et al. [74]. Our analyses design, however, calls for assessing differences between each of the training groups and the control group, or between the 2 training groups. For such 2 × 2 ANOVA design, with the same characteristics as above, 38 participants per intervention group is needed. We therefore plan on a total of 114 participants (38 for each of the three groups) in the final sample. Planning a 30% drop-out rate, we therefore expect to recruit 150 participants (50 for each of the three groups).

### Randomization and allocation

The study will have two training arms and one passive arm. After completing baseline assessment, participants will be randomized to one of the three following arms: the attentional control - Eco-Rescue intervention, the distraction - Bejeweled intervention or the No-training control group. Arm allocation will be concealed to the blinded experimental staff by using computer-generated condition assignment stratified by sex and anxiety score at baseline (assessed by the SCARED-C). To this end we will use the algo detailed in Sella et al. [75]. Such a procedure retains the value of a fully randomly assigned design, while simultaneously minimizing between group variance on the to be matched variables. Randomization will be performed separately for each site. Experimenters blinded to arm allocation will conduct assessments at each timepoint (baseline, post- and follow-up). The experimenters unblinded to the arm allocations will be responsible for administering the general instructions and technical support at any stage of the study and will take care of monitoring participants during the six weeks intervention period. Statistical analyses will be conducted by researchers blind to arm allocation.

### Interventions

#### Attention control training game - Eco-Rescue

*Eco-Rescue* is an action-like game designed and developed collaboratively by [name], [name] and [name] at Campus Biotech Geneva. It is played from a third-person perspective on a PC or laptop. *In Eco-Rescue*, the player takes the role of a pilot tasked to depollute and reforest planets to restore communication and navigation between planets and galaxies. To accomplish this mission, the player will recruit residents of the planet displaying different emotions (i.e., happy, angry, or neutral) to depollute and catch butterflies that will help to reforest planets.

The mechanics of *Eco-Rescue* builds on the Multiple Object Tracking task [53] combined with a dual visual detection task. It requires players to divide, maintain and update the location of faces (with neutral, positive, or negative emotional valence) in visual working memory as they track the movement of different ships and their owners. Concurrently, a detection task requires players to press a key as soon as they detect the apparition of a butterfly to collect it. The stimuli of the detection task can only appear while the ships are moving. By requiring dual-tasking, its game play challenges task-switching abilities as well as the capacity to alternate between different states of attention (focused and distributed) as the game contingency changes, all the while requiring sustained attention.

A key feature of this game is difficulty scaffolding, which refers to the layering of increasingly complex levels of learning objectives in sync with players’ performance. Keeping players in such zone of proximal development has long been known to facilitate learning and video game design excels at doing so [76–78]. The MOT-detection task difficulty is adapted to each player’s performance by adjusting the speed at each number of to-be-tracked moving ships, whereas the difficulty of the detection task remains fixed. The MOT difficulty is adapted through a 3up-1down staircase algorithm programmed to automatically increase or decrease the speed of moving ships to track to maintain player’s performance around 80% accuracy [79, 80].

At each trial, the game provides immediate feedback on correct targets and performance. At the end of each level, the game provides delayed feedback on overall game performance and rewards earning. To avoid automatization of performance and reduce boredom, some variability has been built in. For the detection task, players cannot predict when and where the stimulus will appear on the screen. For the MOT task, the number of targets to track and the number of distractors varies from one trial to another to ensure varied task difficulty.

#### Distraction training game– Bejeweled 3

*Bejeweled 3* is a commercially available puzzle video game, developed and edited by PopCap Games. In this intervention, participants will play on their computer (PC or laptop) via Steam to match the physical setting of the Eco-Rescue attentional control intervention condition.

The main objective of *Bejeweled 3* is to swap adjacent colored gems to create a line or row of 3 or more gems of the same color. The gems so line-up disappear allowing the player to collect points. The goal is to get as many points as possible until it is impossible to swap the gems to line them up. *Bejeweled 3* includes different game modes players can discover freely at their own pace to promote a more enjoyable experience and variability during game sessions (one game usually lasts less than 5 min).

*Bejeweled 3* was chosen as it requires few attentional resources, especially when it comes to divided attention and switches between focused and divided attention (in contrast to *Eco-Rescue)* and because it was reported to reduce stress and anxiety in adult samples [49, 50].

### Outcomes

#### Primary outcome

*Anxiety.* Adolescent anxiety symptoms will be assessed using the Screen for Child Anxiety Related Disorders (SCARED-C [81]). SCARED-C is a 41 items self-report anxiety questionnaire assessing symptoms of Anxiety with subscales measuring General Anxiety Disorder, Social Phobia Disorder, Panic Disorder and Separation Anxiety Disorder. Severity of each symptom is rated referring to the past month on a scale ranging from 0 (Not True or Hardly Ever True) to 2 (Very True or Often True). The total SCARED score will be computed. Higher score indicates higher levels of anxiety.

#### Secondary outcomes

*Attentional control– far-transfer*. Attentional control will be assessed with the Useful Field of View (UFOV) task used by Joëssel [82] and an adaptation of the Test of Variables of Attention (TOVA) as implemented in the ACE-X battery. In the UFOV, participants have to identify whether a briefly flashed smiley presented at the center of the screen has short or long hair and detect on which of the eight cardinal directions was a peripheral target stimulus presented ignoring other distractors. The presentation time is made shorter (more difficult) or longer (less difficult) according to a 3-down-1-up staircase. The task stops after 8 reversals or 72 trials, whichever happens first. Performance is measured by the mean presentation time of the last 5 trials (expressed in milliseconds). This divided attention task measures the efficiency with which attention can be divided over the whole screen and attentional selection still proceeding in the context of distracting information. In the TOVA, participants have to press a response key when presented with a visual stimulus at the top of the screen (go trials) and refrain from responding if flashed at the bottom of the screen (no-go trials). A first block evaluates sustained attention and a second impulsivity. In the sustained attention, go trials represent 25% of the trials; in the impulsivity block, go trials represent 75% of the trials.

*Attentional control– near-transfer.* The Multiple Object Tracking task (MOT) will be used to assess near-transfer of training, given its use in the Eco-Rescue training. The MOT task is similar to the one used by Joëssel [82]. A total of 16 moving circles, including blue (targets) and yellow (distractors), will appear on the computer screen. Participants are presented with an array of yellow smiley faces moving freely within a circular area. During the first two seconds of each trial, a subset of these items is flagged as targets by being blue. The blue smileys then turn yellow and become indistinguishable from the other items. After four seconds, the items stop, one item is highlighted, and the participants have to respond whether this item was initially flagged blue or not. Participants complete a total of 65 trials, 5 trials with 1 target and 12 trials with 2 to 6 targets. MOT performance is measured as the percentage of correct responses (i.e. accuracy) in trials with 3, 4, 5 and 6 targets independently and combined overall. Greater accuracy score indicates better attentional control abilities.

*Affective working memory updating.* Affective working memory updating will be assessed with a modified version of the Affective Backward Digit Span task of Schweizer et al. [83]. Participants are presented with digits (1500ms/digit) in serial order presented on a background of either neutral or affective images to manipulate valence. The images are from the Geneva Affective Picture Database. In each trial, participants are presented with a series of single digits [0–9]. At the end of each trial, participants enter the series of digits seen in reverse order. No feedback is provided as to their answers. In the original version of the task, each span level is presented twice and at least one out of two correct trials per span level is needed for progression to the next level. If both trials are incorrect the task is terminated. In our version, the length of the series to remember is increased or decreased by one digit depending on previous trial success or failure according to a 1-up 1-down staircase algorithm. After two reversals the block stops. This is done once with neutral backgrounds and once with affective background images. Span is estimated for each block as the maximum correct length recalled. The span difference between the two contexts, neutral versus affective is an index of the individual ability to implement attentional control in the face of affective distraction (i.e. affective control).

#### Exploratory outcomes

*Attention Control Self-report*. The Attention Control Scale (ACS [84]) is a 20-item self-report questionnaire designed to measure the construct of attention focusing and of attention shifting. Participants rate items on a 4-point Likert Scale from 1 (almost never) to 4 (always) according to their experience in the past month.

*Emotion Regulation Self-report.* The Cognitive Emotion Regulation Questionnaire (CERQ [85]) will be administered to assess emotion regulation. The CERQ is a 36-item self-report measure that captures stable-dispositional cognitive emotion regulation strategies when people experience stressful or threatening life experiences. Specifically, the following strategies are measured: Self-blame, Blaming others, Acceptance, Refocusing on planning, Positive refocusing, Rumination, Positive reappraisal, Putting into perspective, and Catastrophizing. Participants rate items on a 5-point Likert Scale from 1 (almost never) to 5 (almost always) according to their experience in the past month.

*Depression Self-report*. Participants will complete the modified 8-item version of the Patient Health Questionnaire (PHQ-8 [86]) to assess symptoms of depression at each assessment time point of the study (T1, T2 and T3). Participants are asked to indicate how often they have experienced eight possible problems or symptoms over the last 2 weeks (e.g., “feeling down, depressed, or hopeless,” “feeling tired or having little energy,” and “feeling bad about yourself, or that you are a failure, or have let yourself or your family down”). Each item is rated on a four-item scale (0 - not at all, 1 - several days, 2 - more than half the days, or 3 - nearly every day). Items are summed to obtain scale scores.

*Sleep and Mood Self-report.* Sleep and Mood will be assessed through stand-alone questions for the duration of the training once a week. Sleep: “During the past week, how would you rate your sleep quality overall. This question is rated from 1 (very poor) to 5 (very good). Positive mood: “How much have you experienced positive mood in the past week?” This question is rated from 1 (not at all) to 5 (extremely). Negative mood: “How much have you experienced negative mood in the past week?” This question is rated from 1 (not at all) to 5 (extremely).

*Worry Self-report*. Worry will be assessed with the following statement taken from the Strengths and Difficulties Questionnaire (item 8 from the emotional problems scale [87]) for the duration of the training once a week. “During the past week I worried a lot.” This item is rated 0 (not true), 1 (somewhat true), or 2 (true).

*Intrinsic Motivation Self-report*. Intrinsic motivation for game play will be assessed just at the end of training for the intervention groups only (Eco-Rescue and Bejeweled) using an adapted version of the *Inventory Motivation inventory* (IMI [88]). We will use the same IMI version as in Joëssel [82], that is a 17-item self-report questionnaire with subscales measuring effort/importance, interest/enjoyment, perceived competence, perceived choice and pressure/tension. Participants rate each item on a 7-point Likert scale from 1 (not at all) to 7 (very true), higher score meaning higher motivation.

*Intervention Expectation Self-report*. Expectancy of training intervention on cognition, mood, efficiency and physical fitness will be assessed at post-test (T2) using an adaptation of the Expectation Questionnaire [89]. Participants will indicate on a 5-point Likert scale from 1 (totally disagree) to 5 (totally agree) to what extent the four following statements apply to them regarding their expectations about the study: “I think that participating in this study improved my [1. thinking skills (e.g., memory, attention, speed, reasoning) / 2. mood (e.g. more energetic, less stressed or anxious) / 3. ability to complete different tasks at school and at home (e.g., more efficient in accomplishing my tasks, less procrastination, better coordination with others) / 4. physical fitness].”

### Participant timeline

Participants will be enrolled in the study following eligibility screening, after they approved and signed the consent and assent forms. After completing the baseline assessment (T1) which will include computerized tasks and questionnaires, participants will be randomly assigned to one of the three arms: (1) attentional control - *Eco-Rescue*, (2) distraction - *Bejeweled*, or (3) control - *No-training*.

#### Training and control procedures

Participants in the attentional control (*Eco-Rescue*) and the distraction (*Bejeweled*) conditions will be asked to download the digital platform Steam on their computer to access their allocated games (see below for descriptions). We will ask participants to complete an expected total training time of 12 h, spread over 4 to 8 weeks, preferably distributed in 4 sessions of 30 min each per week for 6 weeks. Participants in the control (*No-training*) condition will live their life as usual during the intervention period. During the training period, every participant will be contacted by an unblinded researcher once a week to maintain contact and will be asked to fill out a self-report questionnaire about worry, sleep and mood. After completing the intervention, participants in the training groups will fill out a questionnaire about their motivation while playing the allocated game (Intrinsic Motivation Inventory -IMI).

Within one week and no less than 24 h after the end of the training phase, participants will complete the post- assessment (T2). Four months after completing their intervention, participants will complete the follow-up assessment (T3). Each assessment point (T1, T2, T3) will last around one hour and a half. Assessments will include as primary outcome the SCARED-C questionnaire, and as secondary outcomes distal and proximal measures of attention (UFOV task and TOVA for distal; MOT task for proximal), as well as a measure of affective control (Affective Backward Digit Span task). As for exploratory outcomes, assessments will include self-report measures of emotion regulation (CERQ), attention (ACS) and of depression (PHQ-8). At the end of follow-up assessment, all participants will fill out a questionnaire measuring their expectations toward the intervention.

**Fig. 1 Fig1:**
[figure not shown]
Flowchart of the proposed randomized controlled trial. Recruitment, screening, and randomization to training will be done online, while baseline, post and follow-up assessments will be administered on sites in either the Geneva or Haifa laboratories

### Adherence and retention

All participants will be compensated in gift cards for each section of the study to incentivize enrollment and study completion. They will receive 10 CHF (or 50 NIS) upon completing each of the baseline-, post- and follow-up assessments (T1, T2 & T3). All participants will be compensated 5 CHF (or 25 NIS) for completing the weekly surveys administered during the intervention phase. To maximize retention, all participants will be told that an additional bonus of 40 CHF (or 200 NIS) will be donated to a charity acting for climate change if they fully complete the study until the follow-up assessment. The two intervention groups (Eco-Rescue and Bejeweled) will be compensated 25 CHF or 175 NIS for completing the entire training.

Retention will be enhanced through weekly phone calls, during which participants will be requested to complete a brief survey. Participants in the training groups (Eco-Rescue and Bejeweled) will be updated on the training time remaining, while participants in the control group (No-training) will be updated on the time remaining before the next assessment.

### Data collection

We expect the study enrolment to begin in January 2024 and we project data collection to be finalized by June 2025 with a total recruitment of 150 participants.

### Data management

All collected data will be coded according to the ethical rules of the institutions collaborating to this project. Because we use secured servers located in Switzerland to acquire behavioural and questionnaire data for both sites, the data of both sites will be consolidated in Geneva. Only a single file on each research site will contain personal identifiable information (e.g., name, date of birth and email) and will be stored separately from other files and securely. Note that this file and the personal information it contains will not be shared between the two sites. This means that no personal information whatsoever will be exchanged between Geneva and Haifa. Personal information will only be used and accessed by the local researchers to contact participants recruited locally for the experiment.

### Risk assessment and monitoring

Whilst we do not expect the occurrence of adverse events or any particular risk to the health or safety of participants - beyond possible boredom or frustration during the activities– we will ask parents and adolescents to report every time an adverse event may occur with the intervention. The research team will be notified, and a decision will be made according to the severity of the adverse event. In case important protocol modifications are made they will be updated on the registration of the trial in clinicaltrials.gov.

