### Study objectives

The aim of this three-arm randomized controlled trial is to evaluate the feasibility of a 6-week video game training intervention to reduce adolescent anxiety-related symptoms. This study will also provide a first window into the efficacy of the proposed treatments when entirely deployed on-line in a young adolescent sample. The first group of participants will receive *Eco-Rescue*, an action game-based intervention (i.e. dual-task training) designed to train attention control. A second group will receive *Bejeweled 3*, a commercialized casual video game (i.e. puzzle game) that does not specifically target attentional control but has shown to reduce anxiety in previous studies, arguably through providing a distraction away from anxious thoughts [49]. A third, no-training control group will not receive any training, providing a needed control for any test-retest effects and allowing us to assess the extent to which the two video game genres proposed may impact self-report and behavioral outcomes (see Fig. 1 for study flowchart).

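### Adverse-event reporting is tied to the intervention, so event counts would not be comparable between the game arms and the No-training arm

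*Protocol article*

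**What the plan says.** Adverse events are dealt with in one short section of the protocol article, Risk assessment and monitoring. The investigators expect nothing beyond boredom or frustration, but "we will ask parents and adolescents to report every time an adverse event may occur with the intervention". The research team is then notified and "a decision will be made according to the severity of the adverse event".

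Training and control procedures says that participants in the No-training "condition will live their life as usual during the intervention period". It also sets up a contact that does not differ by arm: "During the training period, every participant will be contacted by an unblinded researcher once a week to maintain contact". At that contact participants "will be asked to fill out a self-report questionnaire about worry, sleep and mood"; no adverse-event question is mentioned. All arms are assessed at T1, T2 and T3, and "Assessments will include as primary outcome the SCARED-C questionnaire". Under Exploratory outcomes, PHQ-8 is also scheduled at each of these three points.

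Study objectives gives the reason for the third arm: "A third, no-training control group will not receive any training, providing a needed control for any test-retest effects". It is also the reference against which the effects of both games are judged.

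**The concern.** The rule merges two things that are normally kept apart: whether an untoward event happened, and whether the game may have caused it. Families make the second judgement before the first is recorded, and they know whether they were given a game. In a No-training family there is no game for the event to be linked to. The same headache or acute episode of distress could therefore be reported from a game arm and pass unreported in control, simply because of how the request is worded.

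At stake is the safety comparison. The sample is 12- to 14-year-olds selected for raised anxiety, so some untoward events are to be expected without any game. A concurrent randomised control is the natural yardstick for that background, but it serves only if events are looked for in the same way in each arm. Otherwise an excess in the game arms could be real harm or unequal reporting, and the counts could not say which.

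**Working it through.** The article states no adverse-event figure, so there is nothing to reproduce. The check sets the sections side by side.

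**1. Who is asked, and about what.** The request in Risk assessment and monitoring goes to parents and adolescents without restriction by arm. The event itself is described by its link to the intervention. Training and control procedures gives the No-training arm no intervention. The request therefore reaches control families, but what they should report is undefined.

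**2. Who judges the link.** Families do, at the moment of deciding whether to report. They are not blinded; Randomization and allocation describes blinding of the assessing experimenters and the analysts only.

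**3. What is measured equally in all arms.**
- Worry, sleep and mood: weekly during the training period, every participant.
- Anxiety (SCARED-C): T1, T2 and T3, with a look-back of one month.
- Depression (PHQ-8): T1, T2 and T3, with a look-back of two weeks.
- Uptake of other anxiety interventions: screening, post and follow-up (Eligibility criteria).

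Average worsening in these domains can be compared with control whatever the adverse-event rule says.

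**4. What is left over.** First, events that none of these instruments asks about; headache or eye strain would be examples (mine, not the article's). Second, acute episodes between assessments. The weekly items stop when training ends, and T3 comes four months after training. With a one-month look-back, SCARED-C at T3 leaves roughly 4 − 1 = 3 months in which a passing episode would be known only through the adverse-event request.

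**5. Illustration only.** Suppose, as assumptions not found in the documents, that the games do no harm, that the background event rate is equal in all arms, that every event in the game arms is reported and that none is captured in control. With 50 per arm (Sample size), the game arms pooled against control give, by two-sided Fisher exact test:

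| Assumed rate | Game arms | Control captured | p |
|---|---|---|---|
| 5% | 5/100 | 0/50 | 0.17 |
| 10% | 10/100 | 0/50 | 0.031 |
| 20% | 20/100 | 0/50 | 0.0002 |

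With equal capture at 10%, the counts are 10/100 against 5/50 and p = 1.0. If families in the game arms reported only half of their events at 10%, the counts would be 5/100 against 0/50, and p returns to 0.17. The table shows the direction of the distortion at its extreme. It is not an estimate for this trial.

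**The case against.** The strongest reply has four parts.

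**Control reports are not excluded.** A reader might infer that the No-training arm can record no events at all. The text does not say so: the request is not limited by arm, nothing says a control report would be refused, and the article uses the term intervention period for the control arm too. This stands. The wording is ambiguous for control; it does not forbid reports.

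**Worsening is measured anyway.** A reader might also infer that the trial cannot tell game-related harm from background worsening. For anxiety, depression, worry, sleep and mood that is wrong, as step 3 of the working shows. This stands too, and it confines the point to other events and to acute episodes between assessments.

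**No test of adverse events is planned.** The article describes case-by-case decisions by severity and no comparison of events between arms. The Fisher figures cannot therefore be read as false-positive rates of this plan. Nor does the article support the inference that reports would unblind assessors or analysts: Randomization and allocation separates blinded from unblinded staff, and nothing says that the blinded staff receive the reports.

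**An article condenses.** Forms, reporting windows and tabulation may be set out in a full protocol that is not shown, so their absence is no fault. The objection does not remove the point, however, because the article does not merely leave the rule out. It states one, and the stated rule makes reporting depend on presumed cause. It is also fair to note that families are asked to report, so this is a standing request and not purely spontaneous reporting; what is not described is prompting at fixed times.

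**Conclusion.** The point holds in a limited form. As worded, the reporting rule depends on attribution by unblinded families and has no clear meaning in the No-training arm, so adverse-event counts would not be comparable between that arm and the game arms. This matters for events outside SCARED-C, PHQ-8 and the weekly items, and for acute episodes between assessments. It does not touch the primary endpoint or the between-arm comparison of average anxiety, depression, worry, sleep or mood.

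No size can be derived from the documents, because they give no background rate and no reporting rate. The conclusion rests on the wording alone and assumes that families follow the request as written. It is worth correcting because the remedy is cheap and the contacts it needs already exist in every arm.

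**What to change.** Reword Risk assessment and monitoring so that any untoward health event from randomisation to T3 is recorded in all three arms, regardless of presumed cause. Add one identical adverse-event question to the existing weekly contact, which the unblinded researcher already makes, and to T2 and T3. At those two visits unblinded staff should ask it, so that the blinded assessors do not hear about the game. Record the relation to the game as a separate field, after the event itself, and tabulate events by arm.

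The cost is one item at contacts that already take place, plus one table. No extra visits, staff or participants are needed. The downside is that prompting will bring in more minor events than the present request would, in every arm.
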